# Dose REduction strategy of subcutaneous TNF inhibitors in rheumatoid arthritis: design of a pragmatic randomised non inferiority trial, the DRESS study

**DOI:** 10.1186/1471-2474-14-299

**Published:** 2013-10-24

**Keywords:** Rheumatoid arthritis, Dose reduction, Discontinuation, Anti TNF, Spacing, Randomised controlled trial, Non-inferiority, Cost minimalisation, Design, Decremental cost effectiveness ratio (DCER)

## Abstract

**Background:**

Preliminary, mostly uncontrolled studies suggest that dose reduction or discontinuation of tumour necrosis factor blockers can be achieved in a relevant proportion of patients with RA without loss of disease control. However, long term safety, cost effectiveness and feasibility in clinical practice remain uncertain.

**Methods/Design:**

This study is a 18-months pragmatic, non-inferiority, cost minimalisation, randomized controlled trial on dose reduction and discontinuation of the subcutaneous tumour necrosis factor (TNF) blockers adalimumab and etanercept in RA patients with low disease activity. 180 RA patients with low disease activity (DAS28 < 3.2 or clinical judgment of the rheumatologist) are randomized 2:1 to either increased spacing and eventually discontinuation after 6 months of the TNF blocker, and usual care. Implementation is done in routine daily care, using treat to target and feedback implementation in both treatment arms. The primary outcome is non-inferiority (NI margin 20%) in cumulative incidence of persistent (> 3 months) RA flare, according to a recently validated DAS28 based flare criterion (DAS28 change > 1.2, or DAS28 increase of 0.6 and current DAS28 ≥ 3.2). Secondary outcomes include mean disease activity, function, radiographic progression, safety and cost effectiveness. Cost per quality adjusted life year (QALY) differences between groups are expressed as a decremental cost effectiveness ratio (DCER), i.e. saved costs divided by (possible) loss in QALY.

**Discussion:**

The design of this study targeted several clinical and methodological issues on TNF blocker dose de-escalation, including how to taper the TNF blockers, the satisfactory control condition, how to define flare, implementation in clinical practice, and the choice of the non-inferiority margin. Pragmatic cost minimalisation studies using non-inferiority designs and DCERs will become more mainstream as cost effectiveness in healthcare gains importance.

**Trial registration:**

Dutch Trial Register NTR3216, The study has received ethical review board approval (number NL37704.091.11)

## Background

Tumour necrosis factor blocking agents (TNF-blockers) have proven to be effective and safe pharmacological interventions in the treatment of rheumatoid arthritis (RA). As these agents improve clinical, functional and radiographic outcome, TNF-blockers have become an integral part of the standard of care of RA. However, TNF-blockers are also associated with (sometimes dose dependant) adverse effects including injection site reactions, increased risk of infections and non melanoma skin cancer/lymphomas, rare severe adverse events and high costs [1-3]. Optimal use of these drugs is therefore warranted, including the right dose for the right patient [4]. Elective dose reduction in the context of low disease activity is however up to recently very uncommon in daily clinical practice [5].

Emerging data, mostly uncontrolled, has indicated that dose reduction or discontinuation of TNF blockers [6-20] can be achieved in a relevant proportion of patients with RA without loss of disease control. This seems similar between the three most used anti-TNF agents infliximab, adalimumab and etanercept (no data are available on certolizumab and golimumab), although the proportion of patients in whom the drug can be safely tapered seems to depend on the design of the study and context (especially authorized or higher than authorized dosage, dose reduction or stopping, and in early or established RA).

The fact that dose reduction or discontinuation can be successful could be expected for several reasons [4]. In clinical phase II/III studies, lower than registered anti-TNF dosages have been shown to result in good response in sizable proportions of patients [21-23]. So, maintenance of clinical efficacy on lower dosages is to be expected in many patients. In addition, patients sometimes improve independently of the installed treatment, as witnessed by the improvement that is found in placebo arms of clinical trials [21-23]. This improvement is in part spontaneous improvement (regression to the mean) or due to concomitant DMARD or glucocorticoid therapy, but also caused by the placebo effect (expectation bias) [24].

Although data on dose reduction is increasing, a number of aspects of dose tapering strategies in TNF blockers are still not well known thus far. Is reinstallment of the TNF blocker safe and effective? Is reducing the dose while maintaining clinical response associated with more radiographic joint damage in the long-term? Can these strategies be implemented in daily clinical care, and what is the cost effectiveness compared to usual care? To answer these questions, we designed a pragmatic RCT, the results of which will be presented in a separate paper. The primary aim of this study is to demonstrate non-inferiority of a dose reduction strategy compared to usual care with regard to persistent disease flare.

During the design of this RCT, a number of issues had to be addressed and in this paper we would like to describe in detail the study design, and motivate and discuss some of the design choices that were made.

## Methods/Design

This pragmatic, open, randomised, controlled, stratified non-inferiority strategy trial with cost effectiveness analysis is currently being performed (inclusion finished October 2012) at the departments of rheumatology of the Sint Maartenskliniek in the cities of Nijmegen and Woerden, the Netherlands. The study has received ethical review board approval (number NL37704.091.11) and has been registered (Dutch Trial Register NTR3216). A data safety monitoring board (DSMB) is installed. Every three months data on recruitment, efficacy, safety, protocol adherence and protocol updates and all aspects concerning GCP are reviewed with three independent DSMB members, an internal medicin physician, a pharmacist and an epidemiologist.

We made a distinction in an induction phase (months 0-9 after the first dose reduction) and a maintenance phase (months 6-18), because the cost effectiveness is very different between these two time periods [14] (Figure 1). In the induction phase, medication costs are still high, patients are sometimes seen more often, and quality of life might be compromised by temporary flares. Therefore, the cost effectiveness ratio found in the stable maintenance phase can be better interpreted for subsequent years.

**Figure 1 F1:**
[figure not shown]
Design of the induction and maintenance phase.

### Objectives

The aim of the study is to test whether a tight control strategy with protocollised dose reduction and discontinuation in RA patients using TNF blockers is non-inferior with regard to disease control compared to a strategy without dose reduction attempt, and superior with regard to cost effectiveness. This translates in the following research questions:

#### **
*Primary objective*
**

– To assess whether the difference in cumulative incidence in persistent RA flares with a duration > 3 months between the intervention group and the usual care group of RA patients does not exceed the non-inferiority margin of 20% after 18 months of follow up.

#### **
*Secondary objectives*
**

– To compare the cumulative incidence of patients fulfilling flare criteria in the intervention and the usual care group after 9 months and after 18 months of follow up.

– lTo compare the cumulative incidence of patients with persistent RA flare resulting in change of biological between the intervention and the usual care group after 9 months and after 18 months of follow up.

– To compare the proportion of patients with a DAS28 < 3.2, DAS28 < 2.6 and fulfilling remission criteria according to ACR/EULAR criteria between the intervention and usual care group at 9 and 18 months follow up.

– To compare the mean DAS28 and the mean time averaged DAS28 between the intervention and usual care group at 9 and 18 months follow up.

– To compare the proportion of patients using NSAIDs, glucocorticoids or DMARDs between the intervention and usual care group at 9 and 18 months follow up.

– To compare the mean Health assessment questionnaire disability index (HAQ-DI) between intervention and usual care group at 9 and 18 months follow-up.

– To compare the proportion of patients with a change in modified Sharp-van der Heijde Score exceeding the minimal clinical important change (MCIC) between the intervention and usual care group at 18 months.

– To compare the proportion of patients developing adverse events with special attention for allergic/injection reactions between the intervention and usual care group.

– To estimate the decremental cost effectiveness ratio of a protocollised dose reduction/withdrawal strategy of adalimumab or etanercept compared to usual care for the 9 months induction phase and for the 12 months maintenance phase.

#### **
*Study design rationale*
**

The comparison made in this study is between usual care and an alternative strategy (dose reduction) that aims to preserve, but not improve, disease control, whilst minimising the amount of TNF blocker. Therefore, a non-inferiority design (“can we achieve the same effect with less effort”) instead of the classic superiority RCT design (“can we do better with more effort”) was chosen. Of note, this is an adaptation of the original registered research protocol.

#### **
*Study outcome rationale*
**

As disease control is the domain that should remain non-inferior, an outcome measure of disease control had to be selected as primary outcome. Several options come to mind, each with specific advantages and drawbacks.

A straightforward option would be a comparison of disease activity at study end, like for example mean DAS28 with non-inferiority margin of 0.3 DAS28 points. However, it can be expected that at study end no difference is found between the two strategies because patients are treat-to-target, but that flaring is much more frequent during the study in the dose reduction arm. Comparison of time integrated DAS28 might be therefore a better alternative, with the bonus of lower sample size requirements due to the repeated measurements [18]. However, disease activity AUC values are harder to interpret and less informative for a practising clinician than percentage of patients with a flare. The latter also facilitates the calculation of numbers needed to treat/harm (NNT/NNH), thus making results easier to interpret and communicate to patients and physicians alike.

Another option would therefore be to use cumulative incidence of flares as primary outcome, and this is chosen in the majority of dose reduction and discontinuation studies. However, temporary flares that improve after reinstallment of therapy and without a large impact on overall disease control will inevitably occur more frequent in a dose reduction arm, but are clinically less relevant than persisting flares. We therefore chose to assess non-inferiority with respect to cumulative incidence of persisting flare, which is defined as a flare according to the DAS28 based OMERACT validated flare criterion persisting for at least 3 months (independent of treatment changes).

An interesting alternative for a primary outcome of non-inferior disease control would be to prove superior cost effectiveness of the alternative strategy. This would require proving that either the alternative strategy does not lead to loss of Quality Adjusted LifeYears (QALY) but saves costs (dominant strategy), or that the ratio of saved costs and loss of QALY is favourable. Of note, instead of the common term incremental cost effectiveness ratio (ICER), this approach results in a decremental cost effectiveness ratio (DCER), that states the amount of costs saved per lost QALY. The use of this kind of analyses as primary research question is however challenging due to several issues, and therefore very infrequently employed [25]. Firstly, due to the bootstrapping methods that are used to calculate the DCER, a formal sample size calculation is not possible. Secondly, quality of life is only moderately correlated with RA disease activity, posing a real chance of false reinsurance when quality of life does not seem to be compromised. Thirdly, although ICERs of under 40.000 euro per gained QALY are widely accepted as cost-effective , no such clear-cut threshold is available for DCERs. Although the symmetry of using also 40.000 as threshold for DCER seems attractive, as these saved cost can be used elsewhere in health care system to get more quality of life improvement than was lost, it seems awkward to provide suboptimal therapy in relatively low cost effectiveness ranges. However, it can be argued that when the situation was reversed, e.g., when usual care would be to attempt dose reduction, the alternative of continuing medication would not be considered cost-effective when data shows an ICER clearly over 40.000. Interpretation of DCER seems therefore coloured by anchoring to either the existing and/or the alternative strategy. Anyway, a high DCER of for example > 100.000 saved per lost QALY would probably meet wide acceptance from a cost effectiveness point of view [25].

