### Outcome measures

The outcome measures used in this study include disease activity (DAS28CRP based RA Flare criterion, mean and time integrated DAS28CRP), function (HAQ DI), radiological damage (Modified Sharp van der Heijde score, MSvdH), Adverse events (CTC 4.0 criteria), utility (Euroqol 5D 5 L) and costs [33-39].

#### **
*Definition of flare*
**

RA Flare in this study is defined in both treatment arms as a DAS28 increase compared to baseline of more than 1.2 or a DAS28 increase of more than 0.6 with a current DAS28 ≥ 3.2 at two separate timepoints at least 4 weeks apart. This criterion has been validated recently, and has been shown to have the optimal tradeoff between sensitivity and specificity, and the best construct and criterion validity [40]. As it has been shown that flares are frequently temporary and occur and disappear without regimen change, a flare is only considered a flare if it is confirmed after at least 4 weeks [11]. Patients are however not left untreated, and when a flare in disease activity occurs, all bridging therapy including i.a. or im steroids or NSAID can be given and are allowed. Of note, flares are defined with change compared to baseline, not compared to the last visit, to prevent undertreatment in patients with a slight increase in disease in subsequent visits.

When the flare is confirmed after 4 weeks, in both treatment arms patients receive optimal treatment for the flare, for example protocollised reinstallment or dose increase of the TNF blocker or change to another biologic or DMARD. Only patients in whom the flare persist longer than three months (in spite of all treatment intensivation) are classified as having persistent flare, the primary outcome of this study.

#### **
*Secondary outcomes*
**

##### 

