### Randomisation, allocation concealment and blinding

Allocation is stratified for adalimumab and etanercept using stratified block randomization in random sized blocks and a ratio of 2:1. Patients will be randomised by the research physician using a computer-generated randomisation list, which has been transferred to paper sheets and put in sealed envelopes.

This study uses a controlled and randomised, but only partly blinded design, as patients and physicians are not blinded for allocation. Blinding of the assessor performing the joint scores was strived for, and this was done by instructing both patients and the independent joint assessor to first score the DAS28CRP, before assessing medication changes and adverse effects.

Although triple blinding (patients, physicians, researcher) would methodologically be preferable, this is unfeasible because dose reduction in this study is done via increasing the interval instead of decreasing the dosage per injection. The latter would not be sensible, since TNF blockers are given using prefilled injection pens. Blinding of patient and physician is possible when using interval widening, but would be very difficult. The unblinded nature of the study could result in information and attribution bias, as flares in patients in whom the dose is reduced would possible be reported sooner because they would be attributed to the intervention. This bias can however fortunately only lead to overestimation of the drawbacks of a dose reduction strategy, not underestimation, and therefore the higher risk of bias was accepted.

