### Sample size

The null hypothesis in this study is that the intervention is inferior compared to the control arm by more than the non-inferiority margin δ (H0: μ1-μ2 > δ). The alternative hypothesis rejects this null hypothesis (H1: μ1-μ2 ≤ δ), thus proving non-inferiority. The sample size calculation is motivated as follows [42] using the fomula as shown.

$$n_{1}=kn_{2}$$

$$n_{2}=\frac{{\left(Z_{a}+Z_{\beta }\right)}^{2}}{{\left(\epsilon -\delta \right)}^{2}}\left[\frac{p_{1}\left(1-p_{1}\right)}{k}+p_{2}\left(1-p_{2}\right)\right]$$

We estimated that 20% (p_1_ = 0.80) of patients will experience the primary outcome in the usual care arm (persistent flare), with an estimated 15% (p_2_ = 0.85) of patients with this outcome in the intervention arm. Applying one sided testing, an alpha of 0.05 (Z_α_ = 1.64, non-inferiority testing one sided), power 1-beta 0.8 (Z_β_ = 0.84), an inferiority margin of 20% (δ = -0.2), and randomisation ratio of 2:1 intervention versus control (k = 2) resulted in n = 114 and n = 57 for intervention and control arm. Accounting for a 10% drop-out, we choose to include 180 patients in total.

The estimation of proportion of primary outcome in both groups and magnitude of the non-inferiority margin (δ) are motivated as follows. Although clear data are absent, based on the few dose reduction studies that included a control group, and on previously published drug survival curves for adalimumab and etanercept in our population, we estimated that after 18 month in the usual care group 15% of patients would have changed their biologic therapy due to insufficient disease control [12,15,16,28]. We furthermore assumed that 15% of patients in the intervention group can ultimately stop the drug (without persistent flare), resulting in cumulative incidence of 85% flares in the group of patients with partial dose decrease. Of these patients, we estimate that 5% will not respond to reinstallment of the TNF blocker and experience a persistent flare. Thus, we expect a cumulative incidence of persistent flare of 15 + 5 = 20% in the intervention arm.

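### Bridging treatment before flare confirmation can shrink the between-arm difference, so the claim that open-label bias only overstates harm is too broad and the co-medication comparison should be cumulative

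*Protocol article*

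**What the plan says.** The definition of flare (Outcome measures) requires the DAS28 criterion at two timepoints: "a flare is only considered a flare if it is confirmed after at least 4 weeks". The same section says that when disease activity flares, "all bridging therapy including i.a. or im steroids or NSAID can be given and are allowed". The control-arm description (Interventions) also provides for glucocorticoid bridging of a single flare, and the intervention arm receives the same care plus tapering. Bridging before confirmation is thus open to both arms.

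The study outcome rationale expects flares to be much more frequent during the study under dose reduction. It defines the primary outcome, persistent flare, regardless of treatment changes.

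The section on randomisation, allocation concealment and blinding states that neither patients nor physicians are blinded. It notes that flares may be reported sooner when the dose has been reduced, and concludes: "This bias can however fortunately only lead to overestimation of the drawbacks of a dose reduction strategy, not underestimation".

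The only stated between-arm comparison of co-medication is a secondary objective: "To compare the proportion of patients using NSAIDs, glucocorticoids or DMARDs between the intervention and usual care group at 9 and 18 months".

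**The concern.** The confirming DAS28 can be measured while the patient is under the effect of a steroid injection or short course. If the score has dropped below the criterion by then, that episode is not a flare and does not start the count towards persistence. More flares in the intervention arm mean more occasions for this. Because treatment is open and left to the rheumatologist, the threshold for bridging may also differ by arm. Either route lowers the observed difference, which in a non-inferiority trial is the direction that favours the claim.

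The blinding section does not consider this route. Nor is the stated co-medication comparison well suited to reveal it. An intramuscular or intra-articular injection at month 4 need not show up as use at month 9, and background prednisone up to 5 mg is allowed, so current use mixes background with rescue treatment. The trial could report preserved disease control without showing how much of it was held by extra rescue.

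**Working it through.** **Inputs from the Sample size section.** "Applying one sided testing, an alpha of 0.05"; "power 1-beta 0.8"; "an inferiority margin of 20" percentage points; "randomisation ratio of 2:1 intervention versus control (k = 2"). The persistent-flare rates are 20% (intervention) and 15% (usual care). The section first attaches these two rates to the opposite arms. The later derivation is used here because it is the one that reproduces the stated sample size.

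**Reproducing the plan's figure.** With flare-free proportions 0.80 and 0.85:

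n(control) = (1.64 + 0.84)² / (−0.05 + 0.20)² × [0.80 × 0.20 / 2 + 0.85 × 0.15] = 6.1504 / 0.0225 × 0.2075 = 56.7, so 57 control and 114 intervention, as stated.

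**Illustration of masking.** Assumptions, none given in the document:
- True persistent-flare rates lie exactly at the margin, 35% versus 15%.
- All 180 patients are analysed, 120:60.
- A fraction m of persistent flares is never counted.
- The test is the normal-approximation non-inferiority test at one-sided 0.05.

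P(claim) = Φ[(0.20 − d)/SE − 1.645], where d is the observed difference p₁ − p₂ and SE = √[p₁(1 − p₁)/120 + p₂(1 − p₂)/60].

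Equal masking gives d = 0.35(1 − m) − 0.15(1 − m) = 0.20(1 − m). The difference shrinks even when both arms are affected in the same proportion.

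| m | Equal masking: d | SE | P(claim) | Intervention arm only: d | SE | P(claim) |
|---|---|---|---|---|---|---|
| 0 | 0.200 | 0.0634 | 5.0% | 0.200 | 0.0634 | 5.0% |
| 0.10 | 0.180 | 0.0612 | 9.4% | 0.165 | 0.0626 | 13.9% |
| 0.20 | 0.160 | 0.0587 | 16.8% | 0.130 | 0.0617 | 30.5% |
| 0.30 | 0.140 | 0.0558 | 28.5% | 0.095 | 0.0606 | 53.5% |

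Worked row, equal masking, m = 0.10: p₁ = 0.315, p₂ = 0.135, (0.20 − 0.18)/0.0612 = 0.327, and 0.327 − 1.645 = −1.318, so Φ = 0.094.

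The right-hand block is an upper scenario, because bridging is allowed in usual care too.

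**The case against.** The strongest reply is that bridging belongs to the strategy under test. This is a pragmatic trial, both arms may bridge, and the primary outcome deliberately ignores treatment changes and transient flares. A flare that settles with bridging and stays settled is a non-event by design. That stands. It makes the primary outcome defensible, but it does not support a one-directional claim about bias, and it is a reason to report rescue use by arm.

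Four stronger readings are tempting, and the document does not support them.

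- *A bridged flare is lost for good.* DAS28 is measured every 3 months to month 18 against a fixed baseline, so a returning flare can be caught later. Bridging will often delay counting rather than prevent it.
- *The plan denies every bias in favour of dose reduction.* The sentence refers back to information and attribution bias through earlier reporting. The fault is that it generalises from that one mechanism to the direction of open-label bias.
- *The wording proves a snapshot.* A reader might contrast *at* for co-medication with *after* for cumulative incidence, but the same list also uses *at* for time-averaged DAS28. Use at the visit is the natural reading, not a certain one.
- *No planned analysis could show the problem.* Time-averaged DAS28, cumulative flare incidence and costs by arm are partial safeguards. Bridging lowers the first, the second depends on confirmation, and the third does not isolate steroid rescue. The per-protocol analysis does not address the problem, because bridging is permitted.

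The 85% flare figure in the Sample size section says nothing about what share of persistent flares bridging might hide.

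**Conclusion.** The concern holds in a limited form. Bridging before confirmation is allowed in both arms, is likely to be more frequent under dose reduction, and can bias the comparison towards non-inferiority. The statement that open-label bias runs only against dose reduction is therefore too broad. The co-medication comparison, on its natural reading, would miss short courses and injections between visits.

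The size is uncertain. Equal masking of 10% to 30% of persistent flares gives a false non-inferiority rate of 9.4% to 28.5% instead of 5%. Masking in the intervention arm alone gives 13.9% to 53.5%, which should not be read as an expected error rate. Both ranges rest on assumed, permanent masking and on true rates exactly at the margin. Re-detection at later visits would make the real effect smaller.

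**What to change.** 1. Withdraw the claim about the direction of bias, or limit it to earlier flare reporting, and state that bridging before confirmation could act the other way.
2. Define the co-medication comparison for glucocorticoids as cumulative over months 0–9 and 0–18: proportion with at least one bridging course, number of courses, and cumulative exposure, by arm with confidence intervals and separate from stable background prednisone. The cost-effectiveness section already records medication use as a volume of care. That these records hold dates and routes is an assumption to confirm.
3. As a supportive analysis only, treat a criterion-positive visit followed by bridging as a confirmed flare, and judge persistence beyond 3 months from the observed DAS28 at the next scheduled visits. Persistence is not imputed, so a transient flare does not become a primary event merely because it was bridged.

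The cost is some analysis work on data that should already be collected. The drawback is that the supportive analysis will count as confirmed some flares that would have resolved anyway, so it should not replace the primary analysis. No treatment rule changes.
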